### Study outcome measures

This study has two primary outcomes, which reflect 1) pain experience and 2) patient pain management satisfaction. *Pain experience* refers to both pain intensity and pain interference. *Pain intensity* is an assessment of how much a patient hurts. The response categories range from “No pain” to “Very severe” on a 10-point Likert scale [39]. Pain intensity is a relatively homogeneous dimension, and most measures of pain intensity tend to be interchangeable. It was selected because of its relevance to dental patients and practitioners, applicability to all conditions, including acute postoperative dental pain for assessing symptoms, ease of administration, and the relative accuracy with which most adult patients gauge pain. *Pain interference* refers to the extent to which patients have experienced interferences that have prevented them from activities of daily living (ADL), falling asleep, and staying asleep. The response categories range from “Does not interfere” to “Completely interferes” on a 10-point Likert scale. *Patient pain management satisfaction* refers to the level with which patients are satisfied with the overall pain management following their procedure and shared pain management strategies. The response categories range from “Extremely dissatisfied” to “Extremely satisfied” on a 10-point Likert scale. Additionally, it encompasses whether the patient participated in the decision-making regarding their treatment. The response categories range from “Not at All” to “Very Much So” on a 10-point Likert scale.

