### Instruments for data collection

Specific instruments include:mHealth questionnaires

The mHealth Questionnaire #1 includes questions about pre-procedural pain and patient demographics. The mHealth Questionnaire #2 includes questions about pain intensity and pain interference. Pain intensity questions are based on the PROMIS Item Bank v.1.0 – Pain Intensity Scale [39]. On days 1, 3, 5, 7, 14, and 21, patients are asked: “What is your level of pain right now?” On day 7, patients are also asked: “How intense was your pain at its worst since the procedure?” *Pain Interference* questions were taken from the validated Oral Health Impact Profile-14 (OHOP-14) [40] and the Revised American Pain Society Patient Outcome Questionnaire (APS-POQ-R) [41–43] questionnaires to focus attention on the small subset of activities (e.g., sleep) common to post-operative dental patients. If, on days 14 and 21, patients answer the pain intensity question (“What is your level of pain right now?”) as positive (> 0), they will also be asked the six pain interference questions. The mHealth Questionnaire #2 will also collect the following additional information: type and frequency of pain-relief medications taken and the presence of concurrent symptoms such as bleeding, visible swelling, suppuration (pus), and/or fever. The mHealth Questionnaire #3 includes questions from the 2nd mHealth questionnaire and questions about patient pain management satisfaction (see Additional file 1: Appendix 1).2.System Usability Scale (SUS) questionnaire

*FollowApp.Care usability as perceived by patients will be measured* by the system usability scale (SUS) [44–46] questionnaire to measure the usefulness and ease of use of the FollowApp.Care platform. The validated SUS is a simple questionnaire that uses a ten-item attitude Likert scale, giving a global view of subjective usability assessments (see Additional file 2: Appendix 2).3.Unified Theory of Acceptance and Use of Technology (UTAUT)

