### Statistical analysis

Standard descriptive statistics will be used to describe both patient and practitioners’ characteristics using 5 data capture methods: 1) the SUS questionnaire, 2) the mHealth Questionnaire distributed on pre-specified days post procedure, 3) the UTAUT questionnaire, 4) the debriefing/interviews, 5) and the practitioner eCRF. Summary statistics such as means, medians, and ranges will be produced for all measured continuous variables. Frequencies and percent contributions will be computed for all categorical and ordinal variables. Graphical methods like X-charts will examine distributions over time and identify potential, influential time points. The balance of baseline characteristics and measures between groups will be compared using appropriate tests, including chi-squared tests, student t-tests, and Wilcoxon rank-sum tests.

A challenge for this non-randomized study is confounders – pre-existing variables that affect the outcomes and differ between the treatment groups. In order to reduce bias, potential confounders variables will be adjusted in regression models for the analysis. Once participants discontinue the study, they will not be contacted and will not be replaced as the power calculation has accounted for them. If the discontinuation rate is high, the study team PIs will discuss how to proceed with the Network and NIDCR. We will create a missing category for all missing data and assess the need for any imputation methods.

We will estimate the difference in intensity, pain interference, and patient satisfaction dependent on the treatment type. The relative risk (RR) will be the measure of association reported along with 95% confidence intervals. Pain, interference, and satisfaction at the end of the study will be compared among the treatment categories. To model the differential treatment (CDT Grouping) effect on patients’ pain intensity, interference, and satisfaction, on, we will use GLMMs using a Poisson link. Models will include time, treatment type, age, gender, race/ethnicity, medications, and no medication methods as fixed effects. In addition, dentist and Network regions will be included as random effects in the models to account for correlations within clusters.

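### A Poisson mixed model reported as a relative risk is fixed for three bounded rating scores: the estimate is a ratio of mean scores, and its model-based standard errors hold only if variance equals mean

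*Protocol article*

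**What the plan says.** Study outcome measures in the protocol article defines pain intensity, pain interference and satisfaction with pain management as ratings between two labelled ends, each "on a 10-point Likert scale". None is a count, and no cut-off or event is defined for any of them. Instruments for data collection shows that a pain score of zero is possible, because the interference questions on days 14 and 21 depend on a score above zero.

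Statistical analysis gives all three outcomes one model family: "To model the differential treatment (CDT Grouping) effect on patients’ pain intensity, interference, and satisfaction", the text continues, "we will use GLMMs using a Poisson link". The effect measure is also fixed: "The relative risk (RR) will be the measure of association reported along with 95% confidence intervals". Yet the same paragraph opens with a different target: "We will estimate the difference in intensity, pain interference, and patient satisfaction dependent on the treatment type". The listed random effects are dentist and Network region. Sample size states the powered effect in relative terms, as a 20% reduction in pain intensity.

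**The concern.** There are two separate problems.

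The first is what is estimated. Poisson is a distribution, and its usual link is the log. With a log link, the exponentiated coefficient for procedure group is the ratio of mean scores between groups. It would be a relative risk only if the outcome were a yes/no event. The paragraph thus promises a difference, names a risk ratio, and fits a model that yields a ratio of means.

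The second is precision. A Poisson model ties the variance to the mean. A rating with a floor and a ceiling has no reason to obey this. Where the variance exceeds the mean, model-based intervals are too narrow; where it falls below, they are too wide.

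The model serves Hypotheses 1 to 3 and both primary outcomes, so the headline effect and its interval depend on it.

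**Working it through.** **Inputs.** From the article: the scales, the model family, the effect measure, α = 0.05 (two-sided assumed), 3147 enrolled, 40% missing, and 80.0% power for a 20% reduction. Not given: any mean, SD or within-patient correlation. Means and SDs below are assumptions, shown as a range.

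**The plan's own figures.** 3147 × 0.60 = 1888.2, which matches 1888. The 80% power can be neither reproduced nor refuted. For two equal groups of 944 at one time point, 80% power needs SD/mean = 0.20 / [2.802 × √(2/944)] = 1.55. Power is 41% at mean 1, SD 2.5, and over 99% at mean 3, SD 2.5. The power statement therefore does not supply the missing dispersion.

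**Ratio of means against risk ratio.** Simulated 0–10 beta-binomial scores, with the comparison group's mean multiplied by 0.8 and its SD by 0.9:

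| Reference mean, SD | Mean ratio | RR, score ≥ 1 | RR, score ≥ 4 |
|---|---|---|---|
| 2, 2 | 0.80 | 0.89 | 0.71 |
| 3, 2.5 | 0.80 | 0.92 | 0.74 |

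One mean ratio corresponds to different risk ratios, depending on a threshold the article does not define. It also corresponds to different mean differences: 2 − 1.6 = 0.4 and 3 − 2.4 = 0.6.

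**Standard errors.** If the model sets variance = mean, then true SE / model SE = r = √(SD²/mean), and a nominal 5% test has actual type I error 2[1 − Φ(1.96/r)].

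| Outcome | Mean, SD | SD²/mean | r | Type I error |
|---|---|---|---|---|
| Pain | 1, 2 | 4.00 | 2.00 | 33% |
| Pain | 2, 2.5 | 3.12 | 1.77 | 27% |
| Pain | 2, 2.2 | 2.42 | 1.56 | 21% |
| Pain | 2, 1.4 | 0.98 | 0.99 | 4.8% |
| Pain | 3, 2.5 | 2.08 | 1.44 | 17% |
| Pain | 3, 1.6 | 0.85 | 0.92 | 3.4% |
| Pain | 4, 2 | 1.00 | 1.00 | 5.0% |
| Satisfaction | 7, 2 | 0.57 | 0.76 | 0.95% |
| Satisfaction | 8, 2 | 0.50 | 0.71 | 0.56% |
| Satisfaction | 8, 2.5 | 0.78 | 0.88 | 2.7% |
| Satisfaction | 9, 1.5 | 0.25 | 0.50 | 0.01% |
| Satisfaction | 7, 3 | 1.29 | 1.13 | 8.4% |
| Satisfaction | 8, 3.2 | 1.28 | 1.13 | 8.3% |

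At satisfaction 8, SD 2, a comparison that would have 80% power with a correct SE has Φ(2.802 − 1.96/0.707) = Φ(0.03) = 51%.

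**Effect of the bounds.** A Poisson variable with mean 8 puts 18% of its probability above 10; with mean 9, 29%. On a 0–10 scale the largest possible variance is m(10 − m), which exceeds m only if m < 9. So a satisfaction mean of 9 or more cannot be overdispersed.

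**With the variance freed.** Two groups of 400 beta-binomial scores, 1500 runs, seven scenarios. With Poisson SEs, type I error ran from under 0.1% (satisfaction 8, SD 1.5) to 33% (pain 1, SD 2). With robust SEs on the same log-mean model it was 3.8% to 5.5% throughout.

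**The case against.** **The table uses marginal dispersion, and the planned model is conditional.** Variance need equal the mean only after time, procedure, the covariates, dentist and region are accounted for. Many zeros on days 14 and 21 partly reflect a falling mean, which the time effect models. A dentist effect can also absorb excess variance. In a simulation at mean 2, SD 2.2 (150 dentists with 13 patients each, one time point, no true dentist variation), type I error fell from 21% to 5.1% once a dentist effect was fitted, when procedure varied between dentists. At mean 1, SD 2 it fell from 32% to 3.7%; at mean 3, SD 2.5, from 18% to 5.5%. When procedure varied wholly within dentist, it stayed at 21%. The article does not give this mix. The objection stands for the pain figures, which are an upper illustration and not an expected error. It does not help satisfaction if those scores are underdispersed: a random effect can add variance but not remove it.

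**A log link suits the powered effect.** This stands. A 20% reduction is a ratio of means, so the log link need not be replaced.

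**Robust SEs may be in an analysis plan that is not shown.** This stands too: their absence from the article is not the point. The model family and effect measure are stated outright, and no SE method makes a ratio of mean ratings a relative risk.

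**The scale coding.** A reader might infer a contradiction between a 10-point scale and a score of zero, or an open choice of direction. Neither holds: 0–9 has ten points and a zero, and Study outcome measures fixes the direction of the satisfaction scale. What remains is that a ratio depends on the origin. Means of 7 against 8 give 0.875; each coded one point higher, 8 against 9 give 0.889.

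**Conclusion.** The effect label is wrong as written. The planned estimate is a ratio of mean scores called a relative risk, in a paragraph that also promises a difference. This follows from the text alone and needs no assumption.

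The variance assumption fits bounded ratings poorly, and model-based SEs are valid only if it happens to hold. A reader might infer that the SEs are wrong in opposite directions, too small for pain and too large for satisfaction. The documents do not support that as a fact, because they give no mean or SD. Over the assumed values, the SE ratio is about 0.9 to 2.0 for pain means of 1 to 4, and the excess may shrink or vanish where the dentist effect absorbs it. For satisfaction it is about 0.5 to 0.8 with an SD of 2 or less, 0.88 at mean 8 with SD 2.5, and about 1.13 at mean 7 with SD 3 or mean 8 with SD 3.2. Intervals too narrow for low, zero-heavy pain scores and too wide for satisfaction near the top of its scale are the likely pattern, not an established one.

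**What to change.** Take one of two routes, and make the opening sentence about a difference agree with it.

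1. Keep the log link, which matches the powered 20% reduction. Use cluster-robust standard errors, call the estimate a ratio of mean scores, and state each scale's numeric coding.
2. Use a linear or cumulative-logit mixed model and report mean differences or odds ratios.

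Under either route, keep the term relative risk for a defined binary endpoint, such as a score above zero.

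The cost is a change of model and effect-measure wording, with no new data. The second route has one drawback: the reported effect no longer matches the relative effect in the power statement, which would need restating on the new scale.

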## Objectives

### Primary objective is

To assess post-operative pain experiences by dental procedure type through 21 days post-procedure as reported by patients following study-eligible dental procedures and assess patients’ satisfaction with pain management following dental surgical procedures.

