## Hypotheses

The study includes the following hypotheses:

### Hypothesis 1

There is a significant difference in pain intensity measured over time and the dental procedure groupings after adjusting for pain management strategies and other complications. More specifically, are their significant variations in pain intensity due to different treatments after adjusting for:pain management strategy (e.g., pain medications used, adherence to pain management strategy, the usage of non-medicine methods for pain)other complications

### Hypothesis 2

There is a significant difference in pain interference measured over time and the dental procedure groupings, after adjusting for pain management strategies and other complications. More specifically, are their significant variations in pain interference due to different treatments after adjusting for:pain management strategy (e.g., pain medications used, adherence to pain management strategy, the usage of non-medicine methods for pain)other complications

### Hypothesis 3

There is a significant difference in patient satisfaction measured at the end of the 7-day period and dental procedure groupings, after adjusting for pain management strategies and other complications. More specifically, are their significant variations in patient satisfaction due to different treatments after adjusting for:pain management strategy (e.g., pain medications used, adherence to pain management strategy, the usage of non-medicine methods for pain)other complications.

### Hypothesis 4

Reported technology acceptance metrics; performance expectancy (PE), effort expectancy (EE), social influence (SI), and behavioral intention (BI) will be consistent with high acceptance of the FollowApp.Care platform.

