### Sample size

A minimum of 150 and up to 215 dental providers will be recruited, and each provider will be expected to enroll an average of 21 patients for a total of 3147. Assuming a 40% missing data rate among enrolled patients throughout the duration of the study, there will be 1888 patients remaining. This includes patient non-response rates as well as item non-response rates for the outcome of interest during the study period. Given a sample of 1888, the GLMM model for repeated measures will be able to detect a 20% reduction in pain intensity between procedure groups over time with 80.0% power. The minimum sample size was derived by the “longpower” sample package in the R statistical computing environment.

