A secondary analysis will be considered for additional evaluation of the FollowApp.Care platform by the practitioners including assessment of usability and evaluation of fidelity. Means and corresponding estimates of precision (e.g., standard deviations and 95% confidence intervals) and frequency distributions with percentage contributions will be used to report the distribution of each metric. In addition, we will conduct a confirmatory factor analysis (CFA) for multilevel data to test the reliability and construct validity.

All statistical analyses will be performed at the standard significance level (α = 0.05) using R and Stata Statistical Software release 15 for StataCorp LP.

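### The fixed effects named for the pain models include no procedure-by-time term, so they can test an average procedure difference but not one that changes between Day 1 and Day 21

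*Protocol article*

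**What the plan says.** All of the following is in the protocol article.

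- **Primary objective.** It begins: "To assess post-operative pain experiences by dental procedure type through 21 days post-procedure as reported by patients".
- **Hypotheses.** Hypothesis 1 opens: "There is a significant difference in pain intensity measured over time and the dental procedure groupings". Hypothesis 2 uses the same form for pain interference. Each then adds a more specific sentence asking whether the outcome varies with treatment after adjustment for pain management and other complications.
- **Study design.** Pain is recorded on Days 1, 3, 5, 7, 14 and 21.
- **Sample size.** The repeated-measures model is said to "detect a 20% reduction in pain intensity between procedure groups over time", with 80.0% power.
- **Statistical analysis.** The models are GLMMs with a Poisson link, reported as relative risks. The terms are given as: "Models will include time, treatment type, age, gender, race/ethnicity, medications, and no medication methods as fixed effects". Dentist and Network region are random effects. The same section plans a comparison of pain and interference among treatment categories at the end of the study.

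No procedure-by-time term is mentioned anywhere in the article.

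**The concern.** With time and procedure as separate terms on the log scale, every procedure is assumed to follow the same recovery shape, scaled up or down by a constant factor. Nothing in the article supports that assumption across endodontic, periodontal, oral surgery and implant procedures. One procedure may hurt more on the first day and settle quickly, while another starts lower and lingers. The common ratio would then average differences in opposite directions and could sit near 1.

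Two things are at stake. The objective concerns pain by procedure across three weeks, and the named model cannot show how procedures differ in their course. The planned end-of-study comparison is specific to one time, but this model's ratio at Day 21 is by construction its ratio at Day 1.

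**Working it through.** **1. What the named terms imply.** For procedure g at visit t, leaving out covariates and random effects:

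log(mean) = a + b(t) + c(g)

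The ratio of procedure g to procedure h at visit t is exp[c(g) − c(h)]. It contains no t. Four procedure families give three such ratios against a reference, each the same at all six visits.

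**2. What the model returns when trajectories differ.** The means here are illustrative; the article gives none. Assume complete visits, equal numbers at each visit, and no covariates or random effects. The Poisson score equations then make fitted and observed totals agree within each group. Because the fitted ratio is constant, it equals the ratio of the group totals, however time is coded.

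| Day | 1 | 3 | 5 | 7 | 14 | 21 | Total |
|---|---|---|---|---|---|---|---|
| Procedure A | 5 | 3.5 | 2.5 | 1.5 | 0.5 | 0.3 | 13.3 |
| Procedure B | 3 | 3 | 2.8 | 2.2 | 1.3 | 1.0 | 13.3 |

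Model ratio, A to B: 13.3/13.3 = 1.00. Day 1: 5/3 = 1.67. Day 21: 0.3/1.0 = 0.30.

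A second set was fitted as a main-effects Poisson regression. The first group's means were 5, 4, 3, 2, 1, 0.5 (total 15.5) and the second's 4, 3.2, 2.6, 2.2, 1.6, 1.2 (total 14.8).

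- Day-specific ratios, second to first: 0.80, 0.80, 0.87, 1.10, 1.60, 2.40.
- Model ratio: 14.8/15.5 = 0.955.

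As a control, the second group was set to 0.80 times the first at every visit. The model returned 0.80, as it should.

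**3. Does the sample size settle which difference is meant?** The plan's counts reproduce.

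- It states that "each provider will be expected to enroll an average of 21 patients for a total of 3147". 150 × 21 = 3150, against 3147.
- It then says: "Assuming a 40% missing data rate among enrolled patients throughout the duration of the study, there will be 1888 patients remaining". 3147 × 0.60 = 1888.2.

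The claim that the model "will be able to detect a 20% reduction in pain intensity between procedure groups over time with 80.0% power" cannot be reproduced, because no SD, correlation, mean, slope or group sizes are given. As a range, take two equal groups, two-sided α = 0.05, SD 2 to 3 and correlation ρ 0.3 to 0.7, all assumed except α. With m = 6 visits, the days have mean 8.5 and variance 721/6 − 8.5² = 47.92; (1.96 + 0.84)² ≈ 7.85.

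- **20% slope difference**, n per group = 2 × 7.85 × SD² × (1 − ρ) / (m × 47.92 × d²). With slope −0.10 per day (d = 0.02), SD 3 and ρ 0.3, this is 860 per group, 1720 in total. Over slopes −0.10 to −0.14, the total runs from 168 to 1720.
- **20% time-averaged difference**, n per group = 2 × 7.85 × SD² × [1 + (m − 1)ρ] / (m × d²). With mean 2 (d = 0.4), SD 3 and ρ 0.7, this is 663 per group, 1326 in total. Over means 2 to 3, the total runs from 146 to 1326.

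These ranges overlap and ignore clustering by dentist and comparisons among more than two groups. The figure 1888 therefore does not show whether an average or a trajectory was powered.

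**The case against.** A reader might infer that the model cannot test Hypotheses 1 and 2 at all. The article does not support that. The more specific sentence under each hypothesis asks for variation due to treatment, and a joint test of the procedure main effect addresses that on average. In Hypothesis 3 the parallel phrase merely says when satisfaction is measured, so the reference to time in Hypotheses 1 and 2 may mean repeated measurement only. A reader might also infer that the study was powered for a difference in trajectories. The wording permits that, but the working shows that the figure does not establish it.

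The list of terms may also be incomplete. It omits other complications, for which the hypotheses adjust, and baseline pain, which the outcome section names as a covariate. A fuller plan could contain the interaction. This lowers confidence that none is intended. It does not remove the point, because the article states the terms and an end-of-study comparison in the same section, and the two do not fit unless a separate, undescribed analysis is meant.

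The example trajectories were chosen to cross, and the article offers no evidence that real ones do. That is fair: the example shows what the model can hide, not what will happen. The exact 1.00 also needs complete, balanced visits, whereas the plan allows for 40% missing data. The planned graphs of distributions over time may reveal diverging courses, but graphs are neither adjusted contrasts nor a test.

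**Conclusion.** The point holds in a limited form. As named, the fixed effects give each procedure contrast one ratio for Days 1 to 21. The model can test an average procedure difference. It cannot estimate or test a difference that changes over time, nor supply an end-of-study contrast distinct from the Day 1 contrast. It does not follow that Hypotheses 1 and 2 are untestable or that the power statement is wrong.

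The consequence depends on the true trajectories. There is no bias from this source if ratios are constant. If they cross, the model can return a ratio of 1.00 while day-specific ratios run from 1.67 to 0.30, or 0.955 while they run from 0.80 to 2.40; both are illustrations on assumed means. The conclusion assumes that the named terms are the ones to be fitted. Satisfaction is unaffected, since it is measured at Day 7 only.

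**What to change.** 1. **Pain intensity.** Model visit as a categorical factor with a procedure-by-visit interaction. Test Hypothesis 1 with the joint test of procedure plus interaction. Report the interaction test separately, because the joint test alone does not show whether differences change over time. Give adjusted procedure contrasts at every visit; the Day 21 contrast then serves as the end-of-study comparison.
2. **Pain interference.** Do the same over Days 1 to 7. On Days 14 and 21 the interference questions are put only to patients reporting pain above 0 (Instruments for data collection). Include those visits only with a stated rule for patients not asked because their pain was 0; otherwise the contrasts compare only those still in pain.
3. **Sample size.** Say whether the 20% difference is an average or a trajectory difference, and state the inputs used.

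No new data are needed. With four procedure families and six visits, intensity gains (4 − 1) × (6 − 1) = 15 parameters, small against about 1888 patients. Interference over four visits gains (4 − 1) × (4 − 1) = 9. The price is wider intervals for visit-specific contrasts than for one common ratio, and some extra work to define the interference rule.

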## Design and methods

### Study design

POPS is a longitudinal, prospective cohort study that will be conducted with practitioners and their patients undergoing potentially painful dental procedures. Data about baseline pain intensity and patient demographics will be collected prior to the procedure. The patients will receive push notifications through text messages via the FollowApp.Care platform on their mobile devices which asks them to comprehensively record their pain experience at designated time intervals on days 1, 3, 5, 7, 14, and 21 following their procedure. At the end of the 1st week (day 7), they will be asked to report their satisfaction with their post-operative pain management. On Day 23, after the procedure, they will be requested to complete a questionnaire to measure the platform’s usefulness and ease of use. All participating practitioners will be invited to complete a questionnaire to assess the platform’s perceived usefulness and ease of use. A subgroup of practitioners will also be invited to participate in debriefing/interviews to qualitatively evaluate their experiences with using FollowApp.Care for managing their patients’ post-op pain.

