### Study sites

The study is being executed in the National Dental PBRN, a collective network of dental practices that includes private and group practices, public health clinics, community health centers and Federal Qualified Health Centers (FQHCs), academic institutional settings, and special patient population [32]. Since its inception in 2005, the Network has matured into a national network with coverage in urban and rural areas and participation by general dentists, dental specialists, and dental hygienists [33]. The Network is interested in increasing the study and use of HIT to collect PROs within its clinics. It is highly productive, with 19,827 practitioners participating in one or more Network studies [33], and 762 practitioners actively being part of at least one clinical study [34, 35]. The Network has been involved in 58 studies. Practice-based research promotes not only the collection of data at the provider and patient levels but also allows the gathering of patient perspectives before, during, or after the visit. The Network’s infrastructure has matured through various management initiatives into a nimble yet continuous, quality-improvement conscientious network [36]. It is rapidly moving toward achieving the vision of a Learning Health System [37]. Hence, this environment is ideal for developing a practical, focused post-operative pain management study. The six Network geographic regions in the US will be informed of the study protocol and opportunity to participate. We anticipate that all Network practitioners stratified by state, urban/rural, and practice size, will be eligible to participate; between 150 to 215 Network practitioners will be recruited.

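### The stated mixed models for repeated pain intensity and interference have no patient-level term, so standard errors for pooled procedure contrasts are too small where procedures vary within dentists

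*Protocol article*

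**What the plan says.** The Statistical analysis section sets out the model in three steps. For the family: "we will use GLMMs using a Poisson link". For the fixed part: "Models will include time, treatment type, age, gender, race/ethnicity, medications, and no medication methods as fixed effects". For the random part: "dentist and Network regions will be included as random effects in the models to account for correlations within clusters". Patient appears in neither list, and the section mentions no within-patient covariance and no patient-clustered variance.

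The data are repeated within patient. Under Study design, patients are to "record their pain experience at designated time intervals on days 1, 3, 5, 7, 14, and 21 following their procedure", and the Instruments section confirms the six occasions for the current-pain item ("On days 1, 3, 5, 7, 14, and 21, patients are asked"). Interference is collected on the same questionnaires, but on Days 14 and 21 only from patients who report pain above zero. Satisfaction is collected once, on Day 7.

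Hypothesis 1 reads in part: "There is a significant difference in pain intensity measured over time and the dental procedure groupings". Hypothesis 2 has the same form for interference. The Sample size section states that "the GLMM model for repeated measures will be able to detect a 20% reduction in pain intensity".

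**The concern.** Time is a fixed effect, so the model takes one record per visit. Procedure grouping describes the patient's treatment and does not change between visits, so the contrast of interest is between patients. A dentist intercept captures what patients of the same dentist share. It does not capture one patient's tendency to score high or low on every occasion. A Poisson GLMM has no free residual covariance that could absorb this, so without a patient term the model takes a patient's scores as independent once dentist, region and covariates are given.

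At stake are the p-values and confidence intervals for procedure differences in intensity and interference, which together form the pain-experience primary outcome. Standard errors that are too small would lead to too many claims that procedures differ.

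**Working it through.** **The plan's own figures.** The head count reproduces: 3147 × 0.60 = 1888.2, and 150 × 21 = 3150, close to 3147. The 80.0% power cannot be reproduced, because the article gives no mean, standard deviation, within-patient correlation, or number and size of procedure groups. It is neither confirmed nor refuted here, and the check below does not depend on it.

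**Inputs.**
- Scores per patient, m: 6 for intensity (Days 1, 3, 5, 7, 14, 21); 4 for interference in a patient who is pain-free on Days 14 and 21; 3.6 = 6 × 0.60 if the 40% missing data in the Sample size section is spread over visits.
- Significance level: 0.05 from the Statistical analysis section, taken as two-sided (assumption).
- Correlation ρ between scores of the same patient, after allowing for dentist, time and covariates: not in the documents. Assumed range 0.2 to 0.7.

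**Formula.** For a between-patient contrast within dentists, pooled over visits:
- variance understated by DE = 1 + (m − 1)ρ;
- true SE = √DE × model SE;
- true type I error = 2 × [1 − Φ(1.96/√DE)].

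Example with m = 6 and ρ = 0.5: DE = 1 + 5 × 0.5 = 3.5; √3.5 = 1.87; 1.96/1.87 = 1.05; type I error = 0.295. A nominal 95% interval then covers about 70%. Put differently, 1888 × 6 = 11,328 scores carry the information of 11,328/3.5 ≈ 3,237 independent ones.

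| m | ρ | DE | true SE / model SE | true type I error |
|---|---|---|---|---|
| 6 | 0.2 | 2.00 | 1.41 | 0.166 |
| 6 | 0.3 | 2.50 | 1.58 | 0.215 |
| 6 | 0.5 | 3.50 | 1.87 | 0.295 |
| 6 | 0.7 | 4.50 | 2.12 | 0.356 |
| 4 | 0.2 | 1.60 | 1.26 | 0.121 |
| 4 | 0.7 | 3.10 | 1.76 | 0.266 |
| 3.6 | 0.2 | 1.52 | 1.23 | 0.112 |
| 3.6 | 0.3 | 1.78 | 1.33 | 0.142 |
| 3.6 | 0.5 | 2.30 | 1.52 | 0.196 |
| 3.6 | 0.7 | 2.82 | 1.68 | 0.243 |

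The rows for m = 3.6 use an average and are approximate, since patients would differ in how many scores they give.

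**Check by simulation.** Data were generated with no procedure effect: 720 patients under 60 dentists, two procedures mixed within dentist, six scores each. The fitted Poisson model had time, procedure and dentist intercepts (fixed, standing in for random) and no patient term; each setting had 200 runs.
- With no between-patient variation, type I error was 0.06 for Poisson scores and 0.015 for bounded 0–10 scores.
- Once patients differed (observed correlation 0.18 to 0.66), it was 0.125 to 0.555.
- With variance clustered on patient, it was 0.035 to 0.09 across all settings. The Monte Carlo SE at 0.05 is √(0.05 × 0.95/200) ≈ 0.015, so the single 0.09 lies somewhat above nominal.

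The simulation confirms direction and cause. Its larger values exceed the formula, plausibly because the simulated scores also depart from the Poisson mean–variance relation, so the formula range is the one to quote.

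**Where it does not apply.**
- If every dentist performed only one procedure grouping, procedure would be a dentist-level factor. The dentist variance is estimated from the spread of dentist means, which already contains the patient differences, so the inflation would largely vanish.
- A contrast at one visit has m = 1, so DE = 1.
- For changes within a patient over time, positive correlation makes the true variance smaller than independence implies, so the model SE may be too large.

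**The case against.** The strongest reply is that this is a condensed article. The Sample size section calls the model one for repeated measures and uses a longitudinal power package. The sentence on dentist and region does not say that these are the only random effects. A patient term might therefore be intended and be spelled out in a full protocol or analysis plan that is not shown.

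This tempers the point but does not remove it. The article lists the clustering levels and gives their purpose, and the level at which the measurements repeat is absent. That is a stated specification that omits a level, not a detail left unsaid. If another document has the patient term, the article's text still has to be reconciled with it.

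The limits on size stand. The correlation is assumed, and what counts is what remains after adjustment for medications, non-medication methods and demographics. Missing visits reduce the inflation. The mix of procedures within dentists is unknown: eligibility requires only one listed procedure per week, although the Network includes general dentists, so a mix is plausible.

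A reader might infer that every primary test is affected. The documents do not support that: satisfaction is measured once, and the end-of-study comparison uses a single time. Nor can one say flatly that all tests of Hypotheses 1 and 2 are too liberal. The phrase about measurement over time could mean a procedure-by-time contrast, for which the error may run the other way, although the listed fixed effects include no such interaction.

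**Conclusion.** The point holds for the intensity and interference models as written. For procedure contrasts pooled over visits, with procedures varying within dentists, a nominal 5% test has a true type I error of about 17–36% with six scores per patient and about 11–24% with about 3.6. Both ranges rest on an assumed within-patient correlation of 0.2 to 0.7 and a two-sided test. Interference lies towards the smaller end when Days 14 and 21 are skipped because the patient has no pain. Because these are primary-outcome analyses, the wording should be corrected before the models are fitted.

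Two further inferences are tempting and not supported. A reader might conclude that the 80.0% power is wrong, but the article lacks the inputs to test it. A reader might also object to a random effect for region with so few levels ("The six Network geographic regions in the US"). Such a variance is imprecisely estimated, but nothing calculated here shows harm to the procedure contrasts, so it forms no part of this point.

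**What to change.** In the Statistical analysis section, add a patient random intercept nested within dentist, or an equivalent within-patient correlation structure, to the pain-intensity and pain-interference models, and keep the dentist effect. The Day 7 satisfaction model has one record per patient and needs no such term. This also brings the section into line with the repeated-measures description under Sample size. Random slopes over time and cluster-robust standard errors are optional additions.

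The change is about one sentence and needs no new data. The cost is longer run time and wider confidence intervals for the procedure contrasts, which is the correct result where patients' scores are correlated.
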